### Participants

#### Randomization

Participation randomization to either the DaPI or WLC group will be overseen by a research coordinator. Using a simple random technique, each participant will be assigned a unique identification number generated by a random number generator in a 1:1 proportion. Immediately after the participants completed the pre-intervention questionnaire, the research coordinator will notify them of their allocation *via* email.

Participants in the DaPI group will get immediate access to the online program, by logging in with their user ID and password provided by the researcher. They will be able to access the program as per their convenience particularly, their chosen time and day. Meanwhile, participants in the WLC group will be given access to the program after the 1-month follow-up questionnaire has been collected. Figure 1 summarizes the flow of participants in this study. Due to the nature of the intervention, participants and researchers directly involved in the online intervention cannot be blinded to the allocation. Nonetheless, researchers involved in data collection and the analyses will be blinded, as they are not involved in participant allocation or online intervention.

**FIGURE 1 F1:**
[figure not shown]
Participant flow through the study.

#### Study retention

One of the challenges in an intervention study is to retain participants, particularly those allocated to the WLC group. Parents allocated to the WLC group may find it difficult to wait or withdraw from the study by the time they are offered the DaPI program. Parents in both the DaPI and WLC groups will be required to complete questionnaires at three different times (pre- and post-intervention, and 1 month follow-up). Parents in the DaPI group will be required to complete the online program within 8 weeks, whereas those in the WLC group will have a 12-week delayed access to the program. As a means to increase retention, the present study will give parents in both groups an e-voucher worth MYR10 as an incentive for every time they completed a questionnaire (Dumas et al., 2010; Brueton et al., 2017). Parents who withdrew from the study will be contacted to determine the reason for their withdrawal from the program.

#### Sample size and power analysis

A power analysis using the G*Power software (Faul et al., 2007) will be performed in estimating the required sample size. To detect a medium effect size of 0.50, with alpha set at 0.05, and power of 0.80, a minimum sample size of 128 is required. Based on recommendations from Hall and Bierman (2015) review of high attrition from technology-assisted parenting intervention, this study will allow an attrition of 50%, making the target sample size 200, with 100 participants for each group.

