### Statistical analyses

Multivariate analysis of covariance (MANCOVA) will be employed to compare the mean of the outcome variables at pre-assessment, post-assessment, and 1-month follow-up between the two groups (i.e., DaPI vs. WLC). Pairwise comparisons will be performed to identify specific differences in the outcome variables between the groups. Similarly, intention-to-treat analysis (ITT) will be conducted on the data to allow all participants to be included in the analysis, regardless of whether they withdrew from the study or did not complete the intervention. Missing data will be treated using multiple imputations, which is a relatively flexible, general approach for dealing with missing data. The intervention will be considered effective if the parents in the DaPI group show more improvement over time on one of the outcome variables compared to the control group, at a significance level of 0.05, and at small to medium effect size *d* [0.2–0.5].

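### The sample size of 128 is for one univariate comparison, so the stated 0.05 and 0.80 do not jointly describe the MANCOVA and any-one-outcome rule that decide success

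*Protocol article*

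**What the plan says.** The section Sample size and power analysis reports a G*Power calculation: "To detect a medium effect size of 0.50", "with alpha set at 0.05, and power of 0.80, a minimum sample size of 128 is required". It names no test, outcome, assessment time, sidedness or correlation.

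The section Statistical analyses then says: "Multivariate analysis of covariance (MANCOVA) will be employed to compare the mean of the outcome variables at pre-assessment, post-assessment, and 1-month follow-up". Pairwise comparisons between the groups on the outcome variables follow. The intervention counts as effective if its parents "show more improvement over time on one of the outcome variables compared to the control group", at the 0.05 level. No outcome or time is singled out, and no adjustment for multiple outcomes is stated.

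Under Primary outcomes there are three scores: positive parenting, negative parenting and parental self-efficacy. The Secondary outcome section adds two child subscales, behavioral and emotional.

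**The concern.** A power statement belongs to one test at one alpha. Here the calculation fits a single univariate comparison, while the plan decides success across several outcomes and times. Listing the pre-assessment among the compared means also treats baseline as an outcome, so the text does not show what the comparison is adjusted for.

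What is at stake is how the result is read. A null result would be credited with 80% power for d = 0.50, and a positive result on one score with a 5% false-positive risk. The protocol does not show that the deciding procedure has both properties.

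**Working it through.** **Inputs from the protocol article.** Effect size 0.50, alpha 0.05, power 0.80 and N = 128 (Sample size and power analysis); 1:1 allocation (Randomization). **Assumed, because the article gives none:** correlation between scores, baseline-outcome correlation r, and which scores respond.

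**1. Reproduce 128.** Two-sided two-sample t-test, noncentrality d × √(N/4).
- N = 128: 0.5 × √32 = 2.83 on 126 df, power 0.801.
- N = 126: power 0.795, so 128 is the smallest balanced total reaching 0.80.
- An ANOVA, or an ANCOVA with one covariate, at f = 0.25 also gives 128. A one-sided test gives 100 and f = 0.50 gives 34, so neither is the basis.

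No number of outcomes, repeated assessment or correlation enters the calculation.

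**2. If the unadjusted any-one rule decides.** With one score at d = 0.50, the test on that score alone has power 0.801, so the any-one rule has at least that. The price is the chance of at least one false positive. For independent scores it is 1 − 0.95^k; for correlation 0.5 it comes from simulation.

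| Scores k | Correlation 0 | Correlation 0.5 |
|---|---|---|
| 2 | 1 − 0.95² = 0.098 | 0.090 |
| 3 | 1 − 0.95³ = 0.143 | 0.126 |
| 5 | 1 − 0.95⁵ = 0.226 | 0.183 |

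This counts one assessment time only.

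**3. If the MANCOVA decides.** Two-group Hotelling T², noncentral F on p and N − p − 1 df, noncentrality (N/4) × δ′R⁻¹δ with equal correlations; N = 128, one time, no baseline adjustment. Example: three uncorrelated scores with one affected give 32 × 0.25 = 8 and power 0.64; with all three affected, 32 × 0.75 = 24 and power 0.99.

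| Scores, pattern | Corr. 0 | 0.3 | 0.5 | 0.7 |
|---|---|---|---|---|
| 3, all at 0.50 | 0.99 | 0.91 | 0.83 | 0.75 |
| 3, one at 0.50 | 0.64 | 0.71 | 0.83 | 0.96 |
| 5, all at 0.50 | >0.99 | 0.92 | 0.80 | 0.68 |
| 5, one at 0.50 | 0.54 | 0.65 | 0.80 | 0.96 |

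The results fall on both sides of 0.80. Baseline adjustment raises them: with three scores and r = 0.5, the range over these correlations is 0.87 to above 0.99 (all affected) and 0.78 to 0.99 (one affected).

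**4. If adjusted per-score comparisons decide.** Bonferroni split, N = 128, d = 0.50. With baseline as covariate, the effective d is 0.50/√(1 − r²); at r = 0.5 this is 0.50/√0.75 = 0.577.

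| Alpha per score | No baseline adjustment | r = 0.5 |
|---|---|---|
| 0.05 (one score) | 0.80 | 0.90 |
| 0.025 (two scores) | 0.71 | 0.84 |
| 0.0167 (three scores) | 0.66 | 0.80 |

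**The case against.** Four points can be made on the other side.

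- The plan does include pairwise group comparisons on single outcomes, which is the kind of comparison that 128 fits. This stands. However, these comparisons run over several unnamed outcomes and times, and success on any of them counts.
- No multivariate test is written as a gate. Under the any-one rule as worded, 80% is if anything an understatement. This also stands, but then the alpha of 0.05 no longer holds for the rule as a whole.
- A reader might infer that the planned analysis has less than 80% power. The documents do not support that. They give no correlations or effect pattern, and the Objective section expects both parenting behavior and self-efficacy to improve. With all three primary scores at 0.50, MANCOVA power is 0.83 or more up to a correlation of 0.5, although it is 0.75 at 0.7.
- A condensed article may leave the choice of outcome and time to a fuller document. That would excuse silence. Here the article states a power figure, a test and a success rule, and the figure belongs to a different procedure from the rule.

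The t-test label is itself an inference, since the article names no test. The alternatives that give 128 are also single univariate comparisons, so the mismatch does not depend on the label.

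**Conclusion.** The point holds in a limited form. The 128 is correct for one score at one time at two-sided 0.05, and the arithmetic is sound. The pair of 0.05 and 0.80 is not shown for the procedure that decides success: with the unadjusted any-one rule the power survives and the error rate does not, and with the MANCOVA the power is undetermined.

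The sizes rest on equal correlations between scores, one assessment time, complete data on 128 parents and the assumed effect patterns. The defect is one of specification. It does not show that the trial is too small.

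**What to change.** In Statistical analyses, make the deciding test a baseline-adjusted between-group comparison of each named primary score at one named time, with the pre-assessment as a covariate and not as an outcome. State how the alpha is shared if there is more than one such score. The MANCOVA can remain as a supporting analysis.

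In Sample size and power analysis, say that 128 gives 80% power for one such score at two-sided 0.05 without baseline adjustment. If two or three primary scores share the alpha, give the per-score power at 128: 71% or 66% without baseline adjustment, or about 84% or 80% with a stated assumed baseline correlation of 0.5. Do not attach the 80% to the MANCOVA.

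The cost is rewording two short paragraphs and rerunning one calculation. No extra enrolment is needed. The sponsor gives up the freedom to claim success on whichever outcome turns out favourable.

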### Eligibility criteria

Eligible participants will be parents of children aged 10–14 years who are currently living in Malaysia. We aim to recruit 200 parents to participate in the study. Parents from the same household can participate if they focus on a different child within the stipulated age range. It would be an added value to the household if both parents took the opportunity to upgrade their parenting knowledge and skills to improve their children’s development. The inclusion criteria for parents receiving the DaPI would be to have a child within the specified age range and can understand the Malay language. In terms of exclusion criteria, parents who specified that they are currently receiving professional help for their child’s mental health problems will be excluded. No other screening assessments for inclusion or exclusion of the DaPI program will be conducted.

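### A target of 200 does not cover the stated 50% attrition: keeping 128 parents would need 256, and 200 with half lost gives about 70% power, not 80%

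*Protocol article*

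**What the plan says.** The section on sample size and power analysis in the protocol article gives the base calculation: "To detect a medium effect size of 0.50, with alpha set at 0.05, and power of 0.80, a minimum sample size of 128 is required". It then turns to attrition, citing a review of technology-assisted parenting interventions in which attrition was high, and concludes that "this study will allow an attrition of 50%, making the target sample size 200, with 100 participants for each group". The total is repeated under Eligibility criteria ("We aim to recruit 200 parents to participate in the study") and in the Methods part of the abstract, which also gives the 1:1 allocation. Nowhere does the article give another attrition rate or another basis for 200.

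**The concern.** An attrition allowance exists so that the number left after losses still meets the minimum. Here it does not: the minimum is 128, but half of 200 is 100. All the inputs and the result are printed in the same section, so this is a contradiction between stated figures and not a detail left to a fuller document.

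At stake is the power claim. The article presents 200 as the size that protects 80% power at an attrition level it chose to plan for. If that level occurs, the chance of missing a true difference of 0.50 is about 30% instead of 20%, and a null result could be taken as coming from an adequately powered trial. The effect range that the Statistical analyses section uses to call the programme effective, d from 0.2 to 0.5, has the design effect at its upper end. The shortfall therefore bears on the decision the trial is meant to support.

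**Working it through.** **Inputs from the sample size section:** effect size 0.50 (read as a standardised mean difference d), alpha 0.05, power 0.80, minimum 128, attrition 50%, target 200 (100 per group). The 1:1 allocation is from the abstract. **Inferred:** a two-sided, two-sample t-test, since neither the test nor its sidedness is stated.

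**1. The base figure.** A two-sided two-sample t-test (noncentral t) with d = 0.50, alpha 0.05 and power 0.80 needs 63.8 per arm. Rounded up, that is 64 per arm and 2 x 64 = 128 in total, with power 80.1%. The protocol's 128 reproduces. A one-sided test would need 51 per arm (102 in total), which is not the figure printed, so the two-sided reading is the right one.

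**2. The attrition step.** To keep N after losing a fraction a, randomise N / (1 - a):

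128 / (1 - 0.50) = 256, or 128 per arm.

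The common mistake of multiplying by (1 + a) gives 128 x 1.5 = 192. Rounding that up may be where 200 came from, but the article does not say so and the finding does not depend on it.

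**3. What 200 tolerates.** The largest attrition that still leaves 128 is

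(200 - 128) / 200 = 0.36, or 36%.

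**4. What 200 delivers at 50%.** 200 x (1 - 0.50) = 100, or 50 per arm with equal loss. On the same test:

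| Quantity | 64 per arm | 50 per arm |
|---|---|---|
| Power for d = 0.50 | 80.1% | 69.7% |
| d detectable with 80% power | 0.50 | 0.57 |

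The normal approximation gives 70.5% at 50 per arm, so the choice of method does not matter.

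**5. Could covariate adjustment close the gap?** With baseline-outcome correlation r, the effective standardised difference is d / sqrt(1 - r^2). No value of r is given, so the following are assumptions, all with 50 per arm and d = 0.50:

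| Assumed r | Power |
|---|---|
| 0.3 | 74% |
| 0.5 | 82% |
| 0.6 | 87% |
| 0.7 | 93% |

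Power reaches 80% when 0.50 / sqrt(1 - r^2) = 0.566, which gives r = 0.47.

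**The case against.** The arithmetic is not in dispute, but four points can fairly be made against reading too much into it.

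- **The loss of power is conditional.** The section says it allows 50% attrition, not that it expects it. With 40% loss power would be 77.5%, and with 30% loss 83.6%. This stands as a limit on the consequence. The inconsistency remains, because 50% is the rate the section itself uses.
- **Attrition might mean leaving the programme, not missing outcomes.** Under Outcome measures, parents may answer questionnaires without having finished all sessions, and vouchers reward each completed questionnaire. If only the DaPI arm lost half (50 against 100), power would be 81.8%. But the section applies the rate to the size of both arms, including a waitlist arm with no programme to leave before follow-up, and Study retention names that arm as a particular worry. On either reading, 200 does not follow from 128 and 50%.
- **The planned analysis is intention-to-treat with multiple imputation.** Everyone stays in the analysis, but imputation does not by itself restore the information lost with missing outcomes. The protocol also treats attrition as costing sample size; that is why it raises 128 at all.
- **MANCOVA may be more efficient than a t-test.** This is true if baseline is a covariate and r is about 0.47 or more. The article states neither, and its 128 matches an unadjusted comparison. This is a possible repair, not a justification already given.

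The article's condensed form is no defence either, since nothing is missing: the stated figures disagree.

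**Conclusion.** The concern holds. The target of 200 does not follow from a minimum of 128 and 50% attrition: 256 would be needed, a shortfall of 256 - 200 = 56 parents. Equivalently, 200 supports the 80% claim only up to 36% attrition. If half the outcomes are lost in both arms, power for d = 0.50 is about 70% and the detectable effect is d = 0.57.

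The 256 and the 36% need only the protocol's own numbers. The 70% and the 0.57 rest further on the unadjusted, two-sided two-sample t-test that reproduces 128 and on equal loss in the two arms. Baseline adjustment could lift power back to 80% or more, but only under a correlation that the article does not give. The power statement is wrong as written and must be corrected.

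**What to change.** **Recommended: keep 200 and correct the statement.** Suggested text for the sample size section:

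> Randomising 200 parents (100 per group) retains the required 128 if attrition is at most 36%. If attrition reaches 50% in both groups, the 100 parents remaining give about 70% power for d = 0.50 by an unadjusted two-sided t-test, and 80% power for d = 0.57.

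This needs no extra participants. The cost is a less favourable stated power.

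**If 80% power at 50% attrition is to remain the claim,** there are two routes:

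- Raise the target to 256 (128 per group). The cost is recruiting 56 more parents.
- Keep 200 and base the calculation on a baseline-adjusted analysis, naming the baseline covariate and the assumed correlation. It must be at least 0.47 for 80% power with 50 per arm, and it needs support from data on these scales. A value chosen only because it restores 80% would not do.

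Whichever route is taken, state the test and its sidedness, and say whether attrition means missing outcome data or leaving the programme. If the target changes, amend the total in the abstract and under Eligibility criteria as well.

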#### Recruitment

Participants will be recruited across Malaysia through social media (Facebook, Instagram, WhatsApp), government and non-government organizations’ emailing lists, schools, word of mouth, and the study website. Brochures and posters pertaining to the study will be distributed *via* social media and their respective organizations. Consent will be obtained from parents and their respective bodies in the organization prior to their distribution to its members. Interested parents will be able to contact the research team based on contact information on the flyers. Once parents meet the study criteria, they will be provided a link to the online questionnaire. Parents who do not wish to participate or withdraw from the intervention may do so by exiting the online survey and not responding to weekly session reminders.

#### Intervention

DaPI is an adaptation of established evidence-based Western parenting programs, such as Parenting Wisely (Gordon, 2003), Triple-P Positive Parenting Program (Sanders et al., 2000), and the Incredible Years (The Incredible Years, 1984), that focused on parental factors associated with children’s mental health in Malaysia. Considering the diverse ethnicity and religious culture of Malaysia, a parenting module incorporating culturally specific parenting beliefs with local examples would be more suitable for Malaysian parents. As emphasized in previous literature (Hong et al., 2012; Keshavarz et al., 2013; Andrew, 2019; Zulkefly et al., 2021), the parenting beliefs of Asian parents differ from those of the Western construct. For example, Western parents view authoritarian parenting as negative, harsh, and more likely to yield negative outcomes for children. Contrastingly, Asian parents view an authoritarian style as positive style of parenting, where they show care, concern, and involvement through firm control and governance of the child. Furthermore, Asian parents also expect their children’s filial piety and obedience to their families. Contrary to their counterparts from the West, children of authoritarian parents show positive outcomes and feel warmth and care through their parents’ control and firm parenting behavior. Therefore, adjustments and adaptations are needed when using Western programs in the Asian context.

The DaPI can be completed online using a computer, tablet, or smartphone at any time, which is convenient for the parents. The interactive online program will consist of various materials including written information, pre-recorded videos, audio, interactive quizzes, and family activities across the eight sessions. Table 1 presents an overview of each session in the DaPI. The DaPI program will be conducted in Malay, the official language of Malaysia, and will use examples and pictures that represent Malaysian local culture.

**TABLE 1 T1:** Sessions content.

Session number and title	Content overview
1. Normal development and challenges in early adolescence	• Developmental characteristics of early adolescents. • Developmental challenges of early adolescents.
2. Parent-child attachment	• Role of parent-child attachment in child mental health development. • Principles of building secure parent-child attachment relationship.
3. Effective communication	• Role of effective communication in promoting mental health of child. • Principles of effective communication.
4. Parenting behavior and challenges	• Types of parenting behavior. • The effects of parenting behavior on child mental health. • Overcoming parenting challenges.
5. Family cohesiveness	• Role of family cohesiveness. • Strategies to create family cohesiveness.
6. Family conflict	• Overcoming parent-child conflict.
7. Parent mental health	• Negative thinking in parenting • Emotional challenges in parenting • Strategies to challenge parental stress.
8. Child mental health	• Signs and symptoms of child mental health problems. • Helping child overcome negative thinking. • Strategies to help children manage stress.

Parents in the DaPI group will be instructed on effective parenting skills using demonstration, quizzing, recognition, and feedback on correct or incorrect answers *via* an interactive online program. For example, parents will be given a scenario of an adolescent problem and will need to choose one of several solutions, only one of which is an effective method for dealing with this problem. Several review questions will be asked to reinforce the skills learned further.

Session 1 of DaPI will be immediately accessible to parents once they are provided with their login details. New sessions will be available to parents each week in a sequential order upon their completion of the previous session. For example, if a parent is in Week 3 of the DaPI program, the program will unlock session 3 for the parent. However, parents can only start session 3 once they have completed session 2. They are also encouraged to complete one session every week throughout the 8-week program. Each session will take approximately 30 min to complete. Parents will also have the option of saving their progress and returning to continue their sessions at any time, convenient to them. Additionally, parents could self-monitor their progress and receive written feedback from an experienced clinical psychologist on their activities throughout the eight sessions. They can also request support in implementing the intervention techniques from the clinical psychologist by clicking the “chat with me” button.

Several strategies will be employed to engage parents in the DaPI program throughout the 8-week intervention period. Based on earlier studies of online and digital-assisted interventions, a program with frequent reminders and new weekly content would have greater participant usage (Brouwer et al., 2008; Kelders et al., 2012). Automated text messages *via* WhatsApp, SMS, and email will be sent to the participants after completing each module to reinforce the activities. The automated messages also will notify parents of the availability of a new session and prompt them to use the program. Sessions will be considered complete when parents view the summary page of a particular session. Booster reminder emails will be sent after 4 weeks in the program and 1 week before the program ends. If parents in the DaPI program become inactive for a period of 3 weeks, a text message will be sent to check if they are experiencing any technical issues and to boost their interest in continuing with the program.

